### a. Individual-level data

Parasitological data on *Schistosoma* infection among children ages 9-12 were collected prior to each MDA and a year following the last treatment.

In the Sh control studies, 10 ml of urine from a single well-stirred urine sample for each individual was filtered twice, and each of these two filtrations was examined under the microscope; the number of eggs found in each slide and the corresponding volume of urine filtered was recorded.

Parasitological data were also collected in Years 1, 3, and 5 on children in the first-year class and in Years 1 and 5 on adults (see Appendix D). However, given that data on these populations do not represent the primary end-points of the SCORE treatment studies, and that the data collected on them are much more limited than that for 9-12 year olds, they will not be reported as primary end-points.

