## V. DEFINITIONS OF PREVALENCE, INTENSITY, AND COVERAGE

The following definitions will be used for individual-level data:

- Individual mean eggs per 10 ml (Sh studies): Number of eggs found \* 10 / volume of urine filtered. If estimated counts are over 1,000 after volume adjustment, they should be truncated at 1,000. Mean eggs per 10 ml will be used for both analysis and reporting, as this measure is both continuous and a standard metric. Note that some software packages may require mean eggs per 10 ml to be rounded prior to analysis, but this will only affect individuals with less than 10ml of urine filtered.
- Egg positive: a child will be deemed to be egg-positive if one or more eggs were found in any of the slides examined.

The following definitions will be used for reporting on cross-sectional studies:

- **Prevalence of *Schistosoma* infection:** Percentage of egg-positive children among the 9-12 year olds tested in each community each year.
- **Mean intensity of *Schistosoma* infection:** *Arithmetic* mean of individual mean eggs per 10 ml among the 9-12 year-old children. Two values are to be reported:
  - i) Village-level intensity: This is the mean egg count for all tested 9-12 year-old subjects (including those with zero egg counts), which is a measure of community-level contamination potential.
  - ii) Individual-level intensity: This is the mean egg count among egg-positive subjects, which is an estimate of the intensity of infection among known active cases.

- **SBT coverage:** Numbers of school-age children treated / numbers of school-age children.
- **CWT coverage:** Numbers of people in the community treated / number of treatment-eligible people in the community.

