| SHSH vs. SSHH                 | 1.13 (0.76, 1.68)        | 0.55         | 1.02 (0.35, 2.97) | 0.98 |

*Abbreviations:* AMR, arithmetic mean ratio; C, communitywide treatment; H, praziquantel holiday – a year when no praziquantel MDA was provided; PR, prevalence ratio; S, school-based treatment. **Bold** font indicates statistically significant differences.

**Supplemental Table S2:** SCORE's Tanzania Gaining Control Study comparisons of *S. mansoni* infection prevalence and intensity among 9-12 year-old children between study arms at Year 5, adjusted for community level clustering effects, age, and sex

| Study Intervention Comparison | Adjusted prevalence ratio (95% CI) | Adjusted intensity ratio (95% CI) |
|--------------------------------------|-------------------------------------------|------------------------------------------|
| SSSS vs. CCCC                        | 1.09 (0.55, 2.16)                         | 0.96 (0.48, 1.91)                        |
| CCSS vs. CCCC                        | 1.05 (0.55, 2.00)                         | 1.04 (0.51, 2.12)                        |
| CCHH vs. CCCC                        | 1.45 (0.80, 2.69)                         | 1.38 (0.70, 2.72)                        |
| SSHH vs. SSSS                        | 1.33 (0.64, 3.01)                         | 1.91 (0.97, 3.76)                        |
| SHSH vs. SSSS                        | 1.31 (0.63, 2.71)                         | 1.30 (0.61, 2.79)                        |

Abbreviations: C, communitywide treatment; H, praziquantel holiday – a year when no praziquantel MDA was provided; S, school-based treatment.

**Supplemental Table S3:** SCORE's Mozambique Gaining Control Study comparisons of *S. haematobium* infection prevalence and intensity among 9-12 year-old children between study arms at Year 5, adjusted for community level clustering effects, age, and sex

| Study Intervention Comparison | Adjusted prevalence ratio (95% CI) | Adjusted intensity ratio (95% CI) |
|-------------------------------|------------------------------------|-----------------------------------|
| SSSS vs. CCCC                 | 1.01 (0.62, 1.69)                  | 1.62 (0.74, 3.21)                 |
| CCSS vs. CCCC                 | 1.08 (0.69, 1.69)                  | 1.56 (0.76, 3.21)                 |
| CCHH vs. CCCC          | 1.45 (0.85, 2.47)                  | 2.15 (1.10, 4.18)          |

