| Prevalence at Year 5 (%)                                                 | 0.8     | 0.3     | 0.2     | 0.2     | 0.6   | 0.2   | 16.3    | 12.2    | 37.3    | 15.9    | 23.2  | 13.4  | 11.5  | 10.5  |
| Absolute difference between prevalence at Year 5 and baseline            | -3.9    | -5.1    | -1.6    | -2.6    | -3.1  | -4.4  | -5.5    | -11.7   | 7.2     | -3.9    | -1.3  | -9.1  | -2.8  | -12.9 |
| Relative difference between prevalence at Year 5 and baseline (% change) | -83.0   | -94.4   | -88.9   | -92.9   | -83.8 | -95.7 | -25.2   | -49.0   | 23.9    | -19.7   | -5.3  | -40.4 | -19.6 | -55.1 |
| Community-level arithmetic mean infection intensity at baseline          | 1.14    | 0.73    | 0.06    | 0.07    | 0.76  | 0.51  | 3.14    | 6.07    | 6.12    | 3.22    | 4.11  | 5.10  | 1.78  | 5.37  |
| Community-level arithmetic mean infection intensity at Year 5            | 0.20    | 0.07    | 0.01    | 0.01    | 0.13  | 0.05  | 2.05    | 1.16    | 6.89    | 1.84    | 3.61  | 1.39  | 1.37  | 2.18  |
| Egg reduction rate (1-Year 5 intensity/baseline)                         | 82.2%   | 90.4%   | 89.7%   | 90.7%   | 82.4% | 90.4% | 34.8%   | 80.9%   | -12.4%  | 42.8%   | 12.0% | 72.7% | 23.3% | 59.4% |

|                                                                  |      |      |      |      |             |             |      |      |      |      |             |             |             |             |
|------------------------------------------------------------------|------|------|------|------|-------------|-------------|------|------|------|------|-------------|-------------|-------------|-------------|
| Individual-level arithmetic mean infection intensity at baseline | 1.23 | 0.80 | 0.06 | 0.07 | 0.84 | 0.58 | 3.21 | 5.80 | 5.73 | 3.22 | 4.05 | 4.91 | 1.85 | 5.64 |
| Individual-level arithmetic mean infection intensity at Year 5   | 0.21 | 0.07 | 0.01 | 0.01 | 0.14 | 0.05 | 2.09 | 1.16 | 6.72 | 1.78 | 3.61 | 1.37 | 1.37 | 2.20 |

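### Both individual-level intensity rows of Supplemental Table S6 (Niger) average over all tested children, although the SAP defines the measure among egg-positive children only

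*Combined protocol and SAP*

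**What the plan says.** Section V of the Niger SAP asks for two intensity measures. Village-level intensity averages over every tested child aged 9-12, zeros included. The other is defined so: "Individual-level intensity: This is the mean egg count among egg-positive subjects". The positivity rule is that "a child will be deemed to be egg-positive if one or more eggs were found in any of the slides examined", and section III.a states that "10 ml of urine from a single well-stirred urine sample for each individual was filtered twice". Egg counts are scaled to 10 ml of urine. Table 3 of the Niger SAP asks for both measures at baseline and Year 5, and the Preface requires published results to agree with the SAP's definitions.

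Supplemental Table S6 has two community-level rows (the SAP's village-level measure) and two individual-level rows. The first of the latter begins "Individual-level arithmetic mean infection intensity at baseline | 1.23 | 0.80 | 0.06 | 0.07". Neither the title nor the abbreviation note of S6 gives another definition.

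**The concern.** The individual-level values in S6 are almost the same as the community-level values above them (B1 at Year 5 is 3.61 in both), and some are close to zero. A mean restricted to infected children should be several times larger, and where few children are infected it should be very much larger.

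The two measures answer different questions. The all-children mean falls when fewer children are infected, even if those still infected carry as many eggs as before. The egg-positive mean isolates the burden in remaining cases. If the all-children mean stands under the egg-positive label, a reader who applies the SAP definition will take a fall in prevalence for a fall in egg burden among infected children.

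**Working it through.** All inputs are from Supplemental Table S6 (numbers tested, numbers infected, individual-level rows) and the Niger SAP, sections III.a and V.

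**1. Smallest possible value.** One egg in two 10 ml filtrations gives 1 x 10 / 20 = 0.5 eggs/10 ml. A smaller filtered volume only raises this. A mean among positives therefore cannot be below 0.5. Group A shows 0.06 and 0.07 at baseline (SHSS columns) and 0.21, 0.07, 0.01, 0.01, 0.14 and 0.05 at Year 5.

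**2. Which weights reproduce the combined columns.** Combined mean = sum(w x subgroup mean) / sum(w).
- A1 baseline, w = tested: (1.23 x 2,309 + 0.06 x 1,152) / 3,461 = 0.841; stated 0.84.
- A1 baseline, w = infected: (1.23 x 108 + 0.06 x 21) / 129 = 1.04.

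| Cell | Stated | By tested | By infected |
|---|---|---|---|
| A1 baseline | 0.84 | 0.841 | 1.040 |
| A1 Year 5 | 0.14 | 0.142 | 0.192 |
| A2 baseline | 0.58 | 0.574 | 0.662 |
| A2 Year 5 | 0.05 | 0.051 | 0.057 |
| B1 baseline | 4.05 | 4.044 | 4.234 |
| B1 Year 5 | 3.61 | 3.610 | 4.535 |
| B2 baseline | 4.91 | 4.907 | 5.012 |
| B2 Year 5 | 1.37 | 1.372 | 1.410 |

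Allowing 0.005 for rounding of each input and of the stated value, number tested fits all eight cells. Number infected fits only A2 at Year 5.

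**3. Ratio to the community-level rows.** Individual-level divided by community-level lies between 0.94 and 1.14 in every column. A mean among positives should exceed the all-children mean by about tested/infected: 3,461/129 = 26.8 for A1 at baseline and 3,710/22 = 168.6 at Year 5.

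**4. Implied mean among positives** = stated all-children mean x tested / infected. For A1: 0.84 x 3,461 / 129 = 22.5, and 0.14 x 3,710 / 22 = 23.6.

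| Column | Stated, baseline to Year 5 | Change shown | Implied among positives | Implied change | Infected, Year 5 |
|---|---|---|---|---|---|
| A1 | 0.84 to 0.14 | -83% | 22.5 to 23.6 | +5% | 22 |
| A2 | 0.58 to 0.05 | -91% | 12.6 to 20.3 | +61% | 9 |
| B1 | 4.05 to 3.61 | -11% | 16.5 to 15.6 | -6% | 839 |
| B2 | 4.91 to 1.37 | -72% | 21.8 to 10.2 | -53% | 503 |
| C x1 | 1.85 to 1.37 | -26% | 12.9 to 11.9 | -8% | 425 |
| C x2 | 5.64 to 2.20 | -61% | 24.1 to 20.9 | -13% | 392 |

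Rounding alone puts the A1 change between 0 and +9% and the A2 change between +43% and +78%.

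**5. Table S3, SSSS vs CCCC.** An interval built on the log scale has its estimate at the geometric mean of its limits.
- Prevalence ratio 1.01 (0.62, 1.69): sqrt(0.62 x 1.69) = 1.02.
- Intensity ratio 1.62 (0.74, 3.21): sqrt(0.74 x 3.21) = 1.54.
- Row below, CCSS vs CCCC: 1.08 (0.69, 1.69) gives 1.08, and 1.56 (0.76, 3.21) gives 1.56.

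Both upper limits are the same in the two rows. The other eight intervals in S3 are log-symmetric within rounding.

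**The case against.** The figures may be sound and only the label wrong. The pattern fits a mean over individuals placed beside a mean of village means, a distinction that the footnote to Table 3 of the main SAP draws. That is a fair account of how the rows arose, and it makes relabelling a legitimate cure, but it does not meet the Niger definition. Nor are the rows averages of village egg-positive means with zero entered for villages without cases. If villages had about 100 tested children (an assumption), A SHSS x1 at Year 5, with 1,270 tested and 2 infected, would have about 13 villages. One positive village would then give at least 0.5 / 13 = 0.04, against 0.01 stated.

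The consequence is also limited. Primary question 1b of the Niger SAP concerns children aged 9-12 and is not restricted to positives. The egg-positive mean is a descriptive row of Table 3 and does not enter Table 4. This stands. The paper that S6 supports is not among the documents, so no particular statement can be shown to rest on these rows.

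A reader might infer that only prevalence fell throughout the study. The table does not support that. In B2 the implied egg-positive mean fell about 53%, more than prevalence did (40.4%). In B SHSS x1 the stated row rises 17% (5.73 to 6.72), while the implied mean falls about 5%. The absence of a fall is confined to the combined Group A columns, where Year 5 rests on 22 and 9 children. The SHSS columns there have 2 infected children each and are too coarse to judge: for A SHSS x1 rounding alone spans -11% to +216%.

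A reader might also infer that the S3 intervals are wrong in their upper limits and compute replacements from the estimate and lower limit. That presumes those two figures are right and that the interval is log-symmetric. The estimate or the lower limit could equally be the misprint. In Table S2, SSHH vs SSSS, 1.33 (0.64, 3.01), is also asymmetric (midpoint 1.39) with no repeated limit.

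**Conclusion.** The point holds for Table S6. Both individual-level rows are all-children means and contradict definition ii in section V of the Niger SAP, so the egg-positive measure that Table 3 requires is missing from S6. Read under their label, the rows show falls of 83% and 91% in A1 and A2 where the implied egg-positive mean did not fall, and they overstate the falls in B2 and C x2. The rise computed for A2 should not be reported as a finding, since it rests on 9 children and a value stated as 0.05.

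The implied means are approximate. They pool children within a column, use rounded table values, and take the stated rows to be all-children means, as the weight check shows. Exact figures need the individual data. The prevalence, community-level and egg-reduction rows are not affected.

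For Table S3 the repeated limits and the asymmetry justify a check and no more. Both printed intervals include 1, and the documents do not show which figure is in error.

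**What to change.** Recompute both individual-level rows of S6 over egg-positive children from the individual data, with the number of positives beside each mean. Alternatively, relabel the present rows as means over all tested children and add the two rows that the SAP defines. State in a footnote whether each mean pools children or averages village means. Review any text that cites these rows as intensity among infected children.

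Re-extract the SSSS vs CCCC row of S3 from the model output, checking estimate and both limits for both outcomes.

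The cost is two table rows re-run on existing data and one table row verified. No new data or change of model is needed.
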